**Fig. 2 Fig2:**
[figure not shown]
Pictorial schematic of Geko™ device, available from manufacturer’s website at https://www.gekodevices.com/geko-products/hospital-applications-device/

The use of sham stimulation is extremely important in trials of medical devices and has been incorporated into this study. Previous work looking at TTNS, in particular in PD, has suggested a degree of placebo effect with sham stimulation [20], although the improvement was shown to be significantly less than the improvement seen with active stimulation. We have undertaken exploratory work to develop a sham stimulation paradigm that is believable for participants (with sensory feedback experienced) all the while minimising the risk of providing any degree of active tibial nerve stimulation.

#### Intervention description {11a}

The two arms of STRIPE comprise of an active and a sham stimulation protocol. For both arms, participants will be asked to use the Geko™ device for 30 min, twice per week, over a period of 12 weeks. Participants will be trained to use devices in-person at their baseline assessment visit. The first stimulation session will take place at this face-to-face session with training and instruction provided to equip participants to self-administer the intervention at home.

Geko™ provides neuromuscular stimulation at a fixed rate of 1 Hz with a variable pulse width of 35–560 μs using the current T3 model. A single Geko™ device will be used for four stimulation sessions (two weeks) before being replaced with a new device (to mitigate for wear of the electroconductive glue). Between uses, the Geko™ device will be stored adhered to an A4 acetate sheet.

Participants allocated to the active arm will be instructed to place the Geko™ device with the long arm immediately behind the medial malleolus, with the device running parallel along the leg and the writing upright. Stimulation will ideally be titrated to the point of motor stimulation (flexion or fanning of the toes) and participants are encouraged to proceed with the strongest level of motor stimulation that can be comfortably accommodated for 30 min. Alternatively in individuals in whom motor stimulation cannot reliably be provoked, the maximum level of tolerated sensory stimulation will be sought. An inadequate sensory response will be grounds for non-inclusion in the study.

Participants in the sham stimulation arm will be instructed to place the Geko™ device with the long arm on the bony prominence of the lateral malleolus and the device running parallel up the leg along the fibula. Stimulation will be left at the lowest setting, providing a slight sensation without risking depolarising any large nerve fibres. Figure 3 demonstrates visually Geko™ device positioning for each trial arm.

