### Outcomes {12}

Assessment will be obtained from a number of time points. In-person assessment will be carried out at baseline during the initial visit where written consent is formally taken and the first stimulation administered (following completion of baseline assessments). Data will be collected from questionnaires embedded in the participant stimulation diary and further post-intervention questionnaire pack. Participants will also be asked to complete a bladder diary prior to attending their initial visit, as well as in the final week of the intervention period (contained within stimulation diary). The initial bladder diary will be used as a baseline assessment, as well as a screening tool for recruitment. A second follow-up appointment will be undertaken following the intervention period, by telephone/video call and with the use of posted questionnaires and tracked delivery to collect trial materiel (stimulation diaries, follow-up questionnaires, used devices).

Basic demographic information, medication history, relevant co-morbidities and duration of diagnosis will be collected and documented in the case reference file for each participant. Each participant will also have an overall assessment of PD symptoms (Movement Disorder Society – Unified Parkinson’s Disease Rating Scale [21]; MDS-UPDRS) at baseline and lying/standing blood pressures (0- and 3-min time points) assessed at each visit. Table 1 presents a participant timeline for each assessment event.

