## Assignment of interventions: allocation

### Sequence generation {16a}

Eligible participants who have provided informed consent will be randomised to one of two arms (active or sham stimulation). A randomisation sequence using minimisation will be used generated using online software (Sealed Envelope Ltd, London, UK). Age category (18–64 years, > 65 years) and use of a current bladder medication will be used in the minimisation algorithm.

Pre-specified subgroup analysis will be undertaken on participants dependent on their predominant symptom type at baseline, specifically urgency versus nocturia.

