### Methods in analysis to handle protocol non-adherence and any statistical methods to handle missing data {20c}

The primary analysis will relate to the primary outcome measure performed on the intention to treat (ITT) population. A secondary analysis will be performed on the per-protocol population (PP). Secondary outcome measures will also be based on the ITT population. Safety data will be analysed based on the safety population. The Statistical Analysis Plan will be written and agreed prior to data lock. Subjects who fail to complete follow-up assessments will be assessed using a series of sensitivity analyses, using techniques such as last measurement carried forward and multiple imputation methods as appropriate.

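### The sensory-response exclusion appears only in the active-arm procedure and is not tied to a point before randomisation; applied as written, it is a one-arm exclusion after allocation that conflicts with the ITT analysis

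*Protocol article*

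**What the plan says.** All references are to the protocol article.

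- **Active arm, Intervention description {11a}.** The paragraph opens "Participants allocated to the active arm will be instructed to place the" device behind the medial malleolus. It then describes titration towards a motor response, with a fallback: "Alternatively in individuals in whom motor stimulation cannot reliably be provoked, the maximum level of tolerated sensory stimulation will be sought". Its last sentence is the rule at issue: "An inadequate sensory response will be grounds for non-inclusion in the study".
- **Sham arm, same section.** The device sits on the lateral malleolus. "Stimulation will be left at the lowest setting, providing a slight sensation without risking depolarising any large nerve fibres". There is no titration and no adequacy test.
- **Eligibility criteria {10}.** The exclusion list covers ankle abnormality that prevents device placement, but not sensory response.
- **Timing, {11a} and Outcomes {12}.** At the baseline visit, "The first stimulation session will take place at this face-to-face session with training and instruction provided". Consent and baseline assessments precede it. Randomisation is not placed in this sequence.
- **Sequence generation {16a}.** Eligible, consented participants are randomised. No device test is mentioned.
- **Criteria for discontinuing {11b}.** People who discontinue the intervention are asked to continue assessment and are kept in the final analysis.
- **Analysis population {20c}.** "The primary analysis will relate to the primary outcome measure performed on the intention to treat (ITT) population".

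**The concern.** The only sensory response that the article describes eliciting and judging comes from titration at the tibial site, in people already allocated to active. With no sham counterpart, the same person would be not included under one allocation and retained under the other. The judgement would be made by someone who must know the allocation in order to teach the placement. Trial design {8} claims blinding of participants only.

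People with poor sensation at the ankle may differ from the rest in bladder severity or in response. Removing them from one arm would undo the balance that randomisation provides for the week-12 ICIQ-OAB comparison. A later analysis plan cannot fully repair this, because follow-up that was never collected cannot be recovered.

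**Working it through.** **1. Does another section move the rule before allocation?**

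| Section | What it would need to say | What it says |
|---|---|---|
| Eligibility {10} | Sensory response is a criterion | Not listed |
| Consent {26a} | A device test forms part of pre-visit screening | Bladder diary data only |
| Outcomes {12} | A test stimulation precedes randomisation | First stimulation follows baseline assessments; randomisation is not placed |
| Sequence generation {16a} | Randomisation follows a sensory test | Eligible and consented participants, no test mentioned |
| Sham paragraph {11a} | An equivalent rule | None |
| Discontinuation {11b} | Participants who are not included stay in the analysis | Covers those who discontinue; someone not included is not clearly a discontinuer |

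No section does so, and none clearly prevents the rule from acting after allocation.

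**2. The plan's own sample size.** Inputs from Sample size {14}: difference 1 point, SD 2.5, two-sided alpha 0.05, power 80%, attrition 10%.

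- n per arm = 2 × (1.960 + 0.842)² × 2.5² / 1² = 98.1, rounded up to 99
- 99 / 0.9 = 110 per arm, 220 in total

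This matches the stated figure, and the point does not change it.

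**3. Size if the rule acts after allocation and those removed are left out of the analysis.** The documents give neither of the two inputs needed, so both are assumptions:

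- f, the share of the active arm removed: 2% to 15% (about 2 to 17 of 110)
- d, the mean week-12 difference between those removed and those retained: 0.5 to 2.5 points (2.5 is one full SD)

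The full active-arm mean equals the retained mean plus f × d. The sham arm keeps its corresponding participants, so the bias in the arm difference is f × d in size. Starting from 99 evaluable per arm:

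- SE = 2.5 × √(1/(99(1 − f)) + 1/99)
- Two-sided type I error = 1 − Φ(1.96 − bias/SE) + Φ(−1.96 − bias/SE)

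Example, f = 10% and d = 2.5: bias = 0.25, SE = 2.5 × √(1/89.1 + 1/99) = 0.365, bias/SE = 0.685, error = 0.101 + 0.004 = 0.105.

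| f | Bias, d = 0.5 | Type I error | Bias, d = 2.5 | Type I error | Power from lost numbers alone |
|---|---|---|---|---|---|
| 2% | 0.010 | 0.050 | 0.050 | 0.052 | 80.0% |
| 5% | 0.025 | 0.051 | 0.125 | 0.064 | 79.3% |
| 10% | 0.050 | 0.052 | 0.250 | 0.105 | 78.2% |
| 15% | 0.075 | 0.055 | 0.375 | 0.173 | 77.0% |

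With no removals, power at 99 per arm is 80.4%. If f = 0, if d = 0, or if everyone randomised is followed up and analysed, the bias is zero.

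**The case against.** The strongest reply is that non-inclusion is a word about enrolment. It fits a check made before randomisation, and {16a} randomises people who are already eligible. The flow chart (Fig. 1) and the body of the assessment timeline (Table 1), which might show the order, are not in the text available. Nor are the sections on implementing the allocation, on blinding and on the main analysis, and the article condenses a fuller protocol. In addition, {20c} makes ITT primary and {11b} keeps discontinuers, so a randomised poor responder may well be analysed.

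Much of this stands. A reader might infer that participants are in fact removed after allocation in the active arm only, and that the ITT comparison is therefore biased. The documents do not support that: they never state the order of test and randomisation, and never say that such a participant leaves the ITT set. They support neither a particular size nor a direction. The rule applies only when motor response cannot be provoked and the strongest tolerated sensation is also inadequate, so few people may be affected.

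The reply does not remove the defect. The screening reading needs a step that no section describes. It also fits poorly with the sham design, because tibial titration in every candidate would let future sham participants feel active-type stimulation. The text on comparators {6b} and the Discussion stress a believable sham with minimal active stimulation. Even on that reading, an eligibility rule is missing from {10} and sits in one arm's procedure.

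**Conclusion.** The point holds as a fault in what is written. The sensory-response rule is stated for one arm, within the procedure that follows allocation, and is absent from eligibility. Followed literally, it is a differential post-allocation exclusion that conflicts with {20c} and with the intent of {11b}.

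The consequence is conditional. It requires that the rule is applied after allocation, that those affected are left out of the analysis, and that their outcomes differ from the rest. Under the assumed ranges the bias runs from negligible (0.01 points, type I error 5.0%) to serious (0.375 points, 17.3%). The upper end needs both extreme assumptions at once; at 10% removed and a 1-point difference, the bias is 0.10 points and the error 5.9%. The bias favours the device if those removed would have done worse than those retained, and works against it if they would have done better. The case for correction rests on the structure of the rule, not on these figures.

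**What to change.** Reconcile {10}, {11a}, {11b}, {16a} and {20c} so that no one is removed from the study after allocation because of sensory response. State that anyone randomised with an inadequate response is counted as randomised, followed up where possible and included in the ITT set. Recruitment began on 25/10/21 (Trial status), so this should also cover anyone already removed. The cost is a wording change and follow-up of what may be a few people, with slight dilution of the effect.

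If a sensory criterion is kept for eligibility, list it in {10}, apply it identically to every candidate before minimisation, and say so in {16a}. This has a cost of its own: tibial titration before allocation could weaken the believability of the sham, which matters because the primary outcome is self-reported. A test added now would also cover only later recruits.

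Neither route changes the sample size. This point takes no view on what level of stimulation or response is adequate, or on whether a given participant should go on using the device.

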**Fig. 3 Fig3:**
[figure not shown]
Diagram demonstrating positioning of Geko™ device for active and sham stimulation arms

Participants will be encouraged to bring caregivers with them to trial visits to enable them to provide assistance where necessary to optimise concordance, e.g. in achieving correct device placement. This is particularly important because of the dexterity difficulties that occur in Parkinson’s. Therefore, caregivers will be trained along with participants in device placement.

#### Criteria for discontinuing or modifying allocated interventions {11b}

The investigators will discontinue the intervention if they deem that continuation would potentially harm or be detrimental to the participant’s health or well-being.

Reasons for discontinuation include:Voluntary withdrawal from the trialInability to complete assessmentsUnacceptable adverse effects or intercurrent illness as determined by the investigators, in particular causing deviation from treatment scheduleAny change to the participant’s condition justifying discontinuation of treatment

Participants who discontinue the intervention will be asked to remain in the trial and continue assessment if possible. They will be included in final data analysis.

#### Strategies to improve adherence to interventions {11c}

Participants will be assisted as much as possible to remain in the trial and with a dedicated helpline. A follow-up phone call will be undertaken after the first week to assess progress and adherence as well as answer any questions. Participants will also be given a diary booklet for them to document briefly each stimulation session, including whether this was shorter than required.

Bespoke, colour instruction sets will be provided for individuals in each arm of the trial and training sessions tailored to promote correct placement of the device for the relevant arm without compromising believability. Participants will be provided with a fridge magnet documenting the relevant placement position to remind them of optimal technique.

#### Relevant concomitant care permitted or prohibited during the trial {11d}

Pre-existing medications for bladder symptoms and other relevant treatments that may have any influence on bladder function can be continued during the trial period, as long as they are stable without dosing changes. All medications taken by a participant will be recorded in their case record file and any changes made during the period of the study confirmed. Commencing a new relevant medication within the three previous months is a criterion for exclusion but will not preclude recruitment once the 3-month timepoint is reached.

For participants who have been introduced through specialist urology services and are currently considering a specialist treatment such as bladder botulinum toxin, sacral nerve stimulation or catheterisation, recruitment into the study will be dependent on the patient agreeing that this is suspended until completion of the intervention period.

#### Provisions for post-trial care {30}

Any washout effect will be assessed using post-intervention questionnaires following the main interventional period. Usual care for participants will continue to be provided by the UK National Health Service.

### Outcomes {12}

Assessment will be obtained from a number of time points. In-person assessment will be carried out at baseline during the initial visit where written consent is formally taken and the first stimulation administered (following completion of baseline assessments). Data will be collected from questionnaires embedded in the participant stimulation diary and further post-intervention questionnaire pack. Participants will also be asked to complete a bladder diary prior to attending their initial visit, as well as in the final week of the intervention period (contained within stimulation diary). The initial bladder diary will be used as a baseline assessment, as well as a screening tool for recruitment. A second follow-up appointment will be undertaken following the intervention period, by telephone/video call and with the use of posted questionnaires and tracked delivery to collect trial materiel (stimulation diaries, follow-up questionnaires, used devices).

Basic demographic information, medication history, relevant co-morbidities and duration of diagnosis will be collected and documented in the case reference file for each participant. Each participant will also have an overall assessment of PD symptoms (Movement Disorder Society – Unified Parkinson’s Disease Rating Scale [21]; MDS-UPDRS) at baseline and lying/standing blood pressures (0- and 3-min time points) assessed at each visit. Table 1 presents a participant timeline for each assessment event.

**Table 1 Tab1:**
[figure not shown]
Trial assessment procedures throughout the timeline. Participants are seen in person at baseline and week 13 time points. Additional self-completed assessments occur at fortnightly intervals during the intervention period. AE monitoring is performed continually throughout the trial. The primary outcome is assessed at week 12. ^*^Assessments performed before first intervention administered. ^**^Limited to twenty participants

#### Primary outcome

The primary outcome measure will comprise ICIQ-OAB score at week 12, at the end of the interventional period.

ICIQ-OAB was chosen because it relates directly to the predominant modality of bladder symptoms in PD (overactive bladder) and the type of symptoms primarily aided by TTNS interventions. ICIQ-OAB is short to complete, comprising of only four brief questions that aid its repetition to allow monitoring over time whilst minimising participant burden. Data on minimum clinically important difference has also been established for ICIQ-OAB [22]. The ICIQ-OAB score is derived from four questions as part of the large ICIQ male/female lower urinary tract (mLUTS and fLUTS) questionnaires. These have been “recommended with caveats” for use in PD [23]. We will explore potential associations between effectiveness and factors such as disease stage, measured according to the Hoehn and Yahr score, as predefined sub-analyses.

#### Secondary outcomes

Secondary outcome measures will be taken from assessments carried out during in-person visits and bladder diaries at baseline and immediately following intervention. Importantly, this will include the difference in voiding frequency and occurrence of urgency/incontinence episodes. As part of this, participants will undergo non-invasive urodynamic measures and more detailed questionnaire assessment (see Table 2). Amongst these secondary outcomes is a Global Rating of Change Score, based on the question “Compared to before you started, how much difference have the Geko devices made to your bladder symptoms after using them for 12 weeks?”. After baseline, participants will be asked to self-complete the ICIQ-OAB questionnaire fortnightly at home whilst receiving the intervention (weeks 2, 4, 6, 8, 10 and 12) in their stimulation diary booklets. This will be returned by tracked delivery after the virtual follow-up appointment. A further ICIQ-OAB questionnaire pack will be provided to be completed at weeks 16, 20 and 24 in the post-intervention period. A further stamped addressed envelope will be included to return this to the investigators after completion.

**Table 2 Tab2:** List of outcomes and assessment measures with time points

Outcome measure	Assessed by:	Assessed at:
Primary		
Overactive bladder symptoms	ICIQ-OAB part A [24]	Weeks 0–12, 16, 20, 24
Secondary		
Overall patient-perceived benefit	Global Rating of Change score (GRC)	Week 13
Bladder-related quality of life	ICIQ-OAB part B	Weeks 0–12, 16, 20, 24
	ICIQ-OABqol [25]	Week 0,13
Mood	Patient Health Questionnaire (PHQ9-) [26]	Week 0,13
General bladder symptom profile	ICIQ-mLUTS/fLUTS [24, 27] Frequency of incontinence and urgency episodes (bladder diary)	Week 0,13
	Frequency of nocturia (bladder diary)	
Autonomic symptoms	Scales for Outcomes in Parkinson’s Disease- Autonomic (SCOPA-AUT) [28]	Week 0,13
Bowel symptoms	Neurogenic bowel score [29]	Week 0,13
Urodynamic parameters	Post-void residual (ultrasound)	Week 0,13
	Nocturnal polyuria index (bladder diary)	
	Corrected Qmax (uroflowmetery)	
Tolerabillity of Geko™ device	Stimulation Diaries	Throughout intervention period

### Participant timeline {13}

Participant timeline is shown in Table 1.

### Sample size {14}

Sample size for the RCT has been calculated based on preliminary data from a paper by Seth et al. (2018). [18] This demonstrated a significant improvement with tibial nerve stimulation delivered by the Geko™ device with a standard deviation of 2.5. Using their primary outcome measure (ICIQ-OAB questionnaire part A score), which will also serve as the primary outcome for this study, we were able to estimate the required sample size of 110 individuals per trial arm (total *n*= 220). This is based on 80% power, a two-sided significance of 0.05 and ability to detect a 1-point difference in questionnaire score, which has been suggested as the minimum clinically important difference score in some preliminary work [22]. A 10% attrition rate has also been factored in.

### Recruitment {15}

Recruitment will occur from both the PRIME-Parkinson cross-sectional cohort (Bath and surrounding area) and case identification by clinicians both inside and outside of this area. Participants in PRIME-XS have been highly phenotyped including completion of ICIQ mLUTS and fLUTS questionnaire scores for males and females respectively, indicating the presence of bladder symptoms and their nature. Specific scores for urgency and nocturia symptoms will be assessed for these individuals with relevant score thresholds determined to indicate individuals with a potentially appropriate symptom profile to participate. Only PRIME-Parkinson cross-sectional participants who have actively consented to be contacted about further studies will be recruited in this manner (included in the written consent process).

Thresholds for invitation from the PRIME-Parkinson cross-sectional cohort based on ICIQ mLUTS or fLUTS score are:Any one of:Urgency score of “most of the time” or “all of the time” (Question 7a mLUTS, 3a fLUTS)Urgency score of “sometimes” with bother score of 6 or moreSelf-reported nocturia frequency of three times a night or more and NPi of less than 50% from bladder diary (Question 14a mLUTS, 2a fLUTS)

Awareness activities for the STRIPE trial will be undertaken within the region, with all clinicians involved in caring for people with PD approached. This will include neurologists, geriatricians and PD specialist nurses, as well as urologists.

An application will be made for the trial to be advertised on the Parkinson’s UK research directory aimed at patients and awareness of the trial will be raised at research events run by the local branches of Parkinson’s UK. STRIPE will also be advertised by the social media feed of the PRIME-Parkinson portfolio of studies.

